### Primary Outcome Measure

Participants’ treatment expectation will be assessed using the Treatment Expectation Questionnaire [31]. The Treatment Expectation Questionnaire is a generic self-rating scale assessing patients’ outcome and process expectations of medical and psychological treatments on 6 dimensions: treatment benefit, positive impact, adverse events, negative impact, process, and the behavioral control. The questionnaire consists of 15 items that are presented on an 11-point numeric rating scale. For all required analyses, mean subscale scores and the mean total score, each ranging from 0 to 10, will be used. Except for the subscales “adverse events” and “negative impact” with higher scores indicating lower treatment expectations, higher subscale scores indicate higher treatment expectations. Treatment expectation as the primary outcome will be operationalized by the total mean score because it combines process and outcome expectations. To investigate the potential effects of OIC, the impact of OIC on treatment expectations will be additionally analyzed for each of the 6 subscales following an exploratory approach. To counteract the problem of multiple comparisons requiring multiple simultaneous statistical tests, statistical inference will be adjusted using the Bonferroni-Holm correction to reduce the risk of α error inflation.

### Secondary Outcome Measures

The capacity to consent to treatment will be assessed by an adapted German version of the semistructured interview MacArthur Competence Assessment Tool for Treatment (MacCAT-T) [32,33]. Subscale scores, ranging from 0 to 6 (understanding), 0 to 8 (reasoning), 0 to 4 (appreciation), and 0 to 2 (choice), as well as the total sum score, ranging from 0 to 20, will be used for all required analyses. Higher scores indicate higher capacity to consent. Since the MacCAT-T provides a wide range of applications (eg, for dementia), the exact wordings of the questions have been rephrased and adapted to the psychotherapeutic context. Given that risks of psychotherapy may be diverse and multifaceted, it has been deemed sufficient if participants can name 1 risk of psychotherapy instead of 2, as demanded in the original form of the MacCAT-T. Thus, the maximum score of 2 in the item “understanding of benefits and risks” (subscale understanding) can be achieved, even if just 1 risk of psychotherapy can be expressed adequately. The ranges of all subscale scores as well as the range of the total sum score do not change due to this modification.

Decisional conflict will be assessed using the Decisional Conflict Scale [34,35]. The Decisional Conflict Scale consists of 16 items, which are divided into 5 distinct domains: uncertainty, informed, values clarity, support, and effective decision. All items are presented on a 5-point Likert scale, ranging from “not correct at all” to “fully correct.” A total score and 5 subscale scores, each ranging from 0 to 100, will be used for analyses, with higher scores indicating higher decisional conflict. The perceived support in decision-making for or against the utilization of psychotherapy is assessed by 1 self-developed item that is presented on an 11-point Likert scale, ranging from 0 to 10, with higher scores indicating greater perceived support.

Three additional items were developed in advance to assess participants’ (1) expectations about experiencing side effects of psychotherapy, (2) anxiety about experiencing side effects, and (3) expectations about coping with side effects. The corresponding items will be presented on an 11-point Likert scale, ranging from 0 to 10, with higher scores indicating higher expectation about occurring side effects, anxiety about side effects, or respective coping expectations.

The autonomous treatment motivation will be assessed by the translated subscale “autonomous motivation” of the Autonomous and Controlled Motivations for Treatment Questionnaire [36]. The translation from English to German was performed by a native English speaker. The subscale consists of 6 items, which are presented on a 7-point Likert scale, ranging from “strongly disagree” to “strongly agree.” The subscale mean score ranges from 1 to 7, with higher scores indicating higher autonomous treatment motivation, and will be used for all required analyses.

The adherence intention for psychotherapy will be assessed by 3 self-developed items, which will be presented on an 11-point Likert scale, ranging from “not sure at all” to “absolutely sure.” For all required analyses, the mean score will be used, ranging from 0 to 10, with higher scores indicating higher adherence intention.

Seven additional items were developed to assess (1) participants’ interest in psychotherapy as well as their (2) knowledge about psychotherapy in general, (3) what is meant by psychotherapy, (4) the effectiveness of psychotherapy, (5) key mechanisms of psychotherapy, (6) side effects of psychotherapy, and (7) legal and organizational aspects of psychotherapy. The corresponding items will be presented on an 11-point Likert scale, ranging from 0 to 10, with higher scores indicating greater interest or higher knowledge.

The satisfaction with received information will be assessed by an adapted version of the German version of the Client Satisfaction Questionnaire [37,38]. The word “treatment” will be replaced by “received information” to increase the specificity. The 8 items will be presented on a 4-point Likert scale and summed up to a total score, ranging from 8 to 32, with higher scores indicating higher satisfaction with received information.

The information-seeking behavior toward finding a treatment will be assessed by 3 self-developed items, which will be presented on a 7-point Likert scale, ranging from “strongly disagree” to “strongly agree.” The utilization of treatment services will be assessed by 6 self-developed items with the response options “yes” and “no.”

As recently recommended by Papaioannou et al [39], (expected) adverse events and (expected) serious adverse events of OIC and of study participation per se will be assessed at postassessment by using a short interview. In addition to open questions about individual adverse events, 3 a priori developed items about potential adverse events (feeling confused, feeling frightened about potential negative effects of psychotherapy, experiencing doubts about the decision to start psychotherapy) and serious adverse events (suicidal ideation, self-harm, hospitalization) will be assessed. Each event will be rated by the interviewer according to severity (5-point Likert scale) and its potential causal relationship to the study participation (5-point Likert scale). For follow-up assessments (T2 and T3), a self-report will be used instead of an interview.

### Blinding

Due to the nature of the study, neither participants nor the responsible study psychologists can be fully blinded toward the group membership. The assessment and analysis of the capacity to consent and the adverse events, however, will be carried out by researchers who are blinded regarding the randomization and do not otherwise interact with the respective participants throughout the entire course of the study. Questionnaire-based outcomes will be assessed pseudonymously via a web-based software, and the researcher conducting the statistical analyses will be blinded toward the randomized group allocation.

### Bias Control

To reduce heterogeneity in content and risk of performance bias, OIC was manualized and all responsible study psychologists have been specifically trained by a licensed psychotherapist for conducting OIC. A licensed psychotherapist will supervise the study psychologists regarding the conducting of OIC throughout the study. To increase the interrater reliability and to reduce the risk of experimenter bias, all interviewers conducting the MacCAT-T interview have been trained and will be blinded to group allocation. Based on an audio record, an independent and blinded interviewer will conduct a second rating of the MacCAT-T.

### Statistical Analyses

Linear mixed modeling for repeated measures will be conducted for the hypothesis referring to the primary outcome. Following the intention-to-treat approach, all randomized participants will be included in the analysis to avoid attrition bias. The model will contain one between-subject factor treatment (OIC + TAU vs TAU) and one within-subject factor time (T0, T1, and T2). Before linear mixed modeling, additional variables (eg, respective baseline scores, type of prior experiences with psychotherapy, prior knowledge about psychotherapy, satisfaction with the therapeutic relationship, state anxiety, the time of occupation with the information brochure) will be checked for significant associations with the respective outcomes to identify potential covariates. If there are additional covariates, they will be included in the linear mixed model. Group differences will be checked using Tukey posthoc tests. In case of imbalanced group sizes, Bonferroni-corrected posthoc tests will be carried out instead.

The analytical strategy of fitting linear mixed models will also be applied to all analyses, including secondary outcomes. Three exceptions for the described analytical strategy will be analyses including the secondary outcomes of capacity to consent, satisfaction with received information, and (serious) adverse events, for which group differences at postassessment will be examined by an independent sample two-sided *t* test, a Welch *t* test, or a Mann-Whitney *U* test. Intergroup differences at baseline will be detected using independent sample two-sided *t* tests, Welch *t* tests, or Mann-Whitney *U* tests (for continuous variables) and Pearson chi-square tests (for categorical variables). Partial eta squared will be reported for estimating the proportion of explained variance, with *η^2^*=0.01 indicating small, *η^2^*=0.06 indicating moderate, and *η^2^*=0.14 indicating large effects [40]. Cohen *d* will be determined as a measure of effect size for pairwise comparisons (standardized mean differences) by dividing the mean score difference between the groups to be compared by the pooled standard deviation. According to Cohen [40], values of *d*=0.2, *d*=0.5, and *d*=0.8 are considered to indicate small, medium, and large effect sizes, respectively.

Missing values will be imputed using the multiple imputation technique but only if more than 2% of the data is missing. In case of multiple imputation, analyses will be repeated based on per-protocol analyses as a sensitivity analysis. If less than 2% of the data is missing, no multiple imputation will be carried out and a sensitivity analysis will be conducted using the last observation carried forward method. Each hypothesis will be tested two-sided with an α level of .05. All statistical analyses will be performed using SPSS version 27 (IBM Corp).

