In summary, 3 major research gaps can be identified. First, empirical data about whether and how psychotherapists obtain informed consent in clinical practice are sparse. In particular, the integration of risk information has not been investigated so far. Second, there is a lack of concrete implementation strategies for an informed consent procedure that simultaneously accounts for legal, ethical, and clinical functionalities. Third, the effects of informed consent procedures on factors contributing to psychotherapy outcomes have not yet been investigated systematically. The latter 2 research gaps will be specifically targeted in this study. An optimized informed consent consultation (OIC) for psychotherapy has been developed as a new clinical tool based on the most recent empirical evidence. OIC will be applied in a web-based context for 2 reasons: (1) to increase accessibility and (2) to reduce health risks due to the ongoing pandemic. As the web-based context requires access to the internet for all participants and the study staff, potential interferences due to internet connection problems will be considered by providing clear instructions to participants with backup weblinks and contact information via phone.

This study aims to investigate the efficacy of OIC for persons with an indication for psychotherapy. We hypothesize that treatment expectations, autonomous treatment motivation, and adherence intention increase to a greater extent in the OIC condition than in the treatment as usual (TAU) condition from baseline (T0) to the follow-up assessment (T2). Moreover, we assume that decisional conflicts and expectations about the side effects of psychotherapy decrease to a greater extent in the OIC condition than in the TAU condition from baseline (T0) to the follow-up assessment (T2).

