#### Sample Size

The required sample size was a priori calculated using the G*Power software. Based on a previous experimental study analyzing the effects of framing and personalizing information about endocrine treatment on side-effect expectations in healthy women [14], a small-to-medium effect size can be expected for the impact of OIC on the primary outcome (treatment expectations). For two-tailed testing and a predetermined α level of .05, 106 participants would provide 80% power to detect significant interaction and the main effects of Cohen *f*=0.125 on the primary outcome. To compensate for an anticipated dropout rate of 15%, a total sample of 122 participants will be randomly assigned to one of the 2 groups (n=61 per group). Since it is assumed that at least 50% of all individuals can be included in the clinical trial after screening, approximately 244 individuals will need to be screened (see Figure 1).

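### The hypotheses concern T0-to-T2 change, but no T0-T2 contrast is named as the deciding test, and N=106 best matches an overall interaction that a T1-only effect could make significant

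*Protocol article*

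**What the plan says.** The Introduction predicts that treatment expectations (the primary outcome), autonomous motivation and adherence intention will "increase to a greater extent in the OIC condition than in the treatment as usual (TAU) condition from baseline (T0) to the follow-up assessment (T2"). It predicts a greater decrease over the same interval for decisional conflict and side-effect expectations.

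Statistical Analyses describes the model for the primary hypothesis: "The model will contain one between-subject factor treatment (OIC + TAU vs TAU) and one within-subject factor time (T0, T1, and T2"). It adds: "Group differences will be checked using Tukey posthoc tests", with a Bonferroni version if group sizes are imbalanced. It does not say at which time points these tests are made, and it names no T0-T2 contrast. It also says: "Each hypothesis will be tested two-sided with an α level of .05".

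Sample Size states that "106 participants would provide 80% power to detect significant interaction and the main effects" at Cohen f = 0.125, two-tailed, alpha .05.

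Primary Outcome Measure fixes the score (the TEX-Q total mean) but no time point. Under Procedure, OIC is given at the T1 visit, the post-assessment follows at that same visit, and T2 comes two weeks later. Blinding acknowledges that participants cannot be fully blinded.

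**The concern.** A larger change from T0 to T2 in one arm is a single contrast with one degree of freedom. A model with a three-level time factor can supply that contrast. It also supplies an overall treatment-by-time interaction (2 df), a treatment main effect, a time main effect and a T1 contrast. The protocol does not say which of these decides the primary hypothesis, and the sample size text points away from the T0-T2 contrast.

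The choice matters because the overall interaction does not distinguish between patterns. It responds equally to a difference at T1 only, at T2 only, or at both. T1 is an unblinded self-report taken at the visit where the consultation has just been given, so it cannot show that an effect lasts. The treatment main effect does not isolate the hypothesis either, because it averages in T0, where randomization makes the arms equal in expectation.

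At stake is what a positive result means: a shift reported just after the consultation, or one still present two weeks later. The same ambiguity applies to the four secondary hypotheses in the Introduction.

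**Working it through.** **Inputs.** From the protocol: f = 0.125, two-sided alpha .05, 80% power, N = 106, two arms allocated 1:1 (53 per arm), time levels T0, T1 and T2. Assumed, because not stated: within-person correlation rho = 0.5, sphericity, and equal variance at each time. Rho is varied below.

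**Step 1: reproduce N = 106.** For the treatment-by-time interaction with m time points and two arms, the noncentral F has lambda = f² × N × m / (1 − rho), df1 = m − 1 and df2 = (N − 2)(m − 1).

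For m = 3: lambda = 0.015625 × 106 × 3 / 0.5 = 9.94, with df 2 and 208. Power is 80.7%. N = 104 gives 79.9%, so 106 is the smallest even N that reaches 80%.

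| Test at f = 0.125, rho = 0.5 | Smallest even N for 80% | Power at N = 106 |
|---|---|---|
| Interaction, 2 time points | 128 | 72.2% |
| Interaction, 3 time points | **106** | **80.7%** |
| Interaction, 4 time points | 90 | 87.3% |
| Treatment main effect, 3 time points | 338 | 34.5% |

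The three-time interaction is the best match, and it agrees with the three time levels in Statistical Analyses. It is not proven: two time points with rho = 0.59 also give 106.

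**Step 2: translate f into an arm difference.** Let the arm differences at (T0, T1, T2) be D, in SD units. Then f² = Σ(D − mean D)² / (4 × 3). For each of the patterns (0, d, 0), (0, 0, d) and (0, d, d), the sum is (2/3)d², so f = d × √(1/18) = 0.2357d. Setting f = 0.125 gives d = 0.53 SD in all three cases. The interaction therefore has the same power for a transient, a delayed and a sustained effect.

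**Step 3: an effect at T1 only** (N = 106).

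| Difference at T1, zero at T2 | rho | Interaction significant | T0-T2 contrast significant |
|---|---|---|---|
| 0.53 SD | 0.3 | 65.5% | 5% |
| 0.53 SD | 0.5 | 80.7% | 5% |
| 0.53 SD | 0.7 | 96.0% | 5% |
| 0.40 SD | 0.5 | 55.1% | 5% |
| 0.30 SD | 0.5 | 33.4% | 5% |

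A simulation of 20,000 trials at 0.53 SD and rho = 0.5 gave 80.6% for the interaction and 5.0% for the contrast.

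**Step 4: an effect that halves by T2.** With 0.61 SD at T1 and 0.31 SD at T2 (again f = 0.125, rho = 0.5), the interaction has 80.7% power. The T0-T2 contrast has 34.8%.

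**Step 5: power of the hypothesised contrast** for a sustained 0.53 SD effect, 53 per arm, rho = 0.5.

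- Unadjusted change: SE = √(2 × 2(1 − 0.5)/53) = 0.194, and 0.530/0.194 = 2.73. Power is 77.2% with 104 df, or 77.6% with the pooled mixed-model error (208 df).
- Baseline-adjusted T2 difference: SE = √(2 × (1 − 0.25)/53) = 0.168, and 0.530/0.168 = 3.15. Power is about 88%.

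**The case against.** The strongest case against is that the protocol never makes the overall interaction the deciding test. Statistical Analyses lists two factors and does not use the word interaction; it appears only in Sample Size, paired with main effects. Each hypothesis is to be tested, and the hypotheses are those in the Introduction, so the authors may intend the T0-T2 contrast, which their model can supply. A reader might infer that a T1-only effect *would* be declared as the follow-up benefit. The text does not support that: no decision rule is written, so it only *could* be. Nor does N = 106 prove which test was powered, since the match depends on an unstated correlation.

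A second objection is that post hoc group comparisons, if made at each time point, would expose an absent T2 difference. That also stands. With the arms equal at T0 in expectation, the T2 difference and the difference in T0-to-T2 change are the same estimand. But the protocol does not say when these comparisons are made, and it does not make a T2 difference a condition for success.

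Third, the plain change contrast has slightly less power than the interaction for a sustained effect (about 77% against 81%). Changing the contrast alone therefore gains no power; the gain to 88% comes from baseline adjustment, a separate modelling choice. The T1-only scenario is illustrative, and no figure in the protocol predicts it.

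Finally, choosing a contrast is often left to an analysis plan. That does not dispose of the point. The article states one estimand and gives a sample size that best fits a test which does not isolate it. This is a mismatch within the document, not only a missing detail.

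**Conclusion.** The concern holds in a bounded form. The hypotheses are T0-to-T2 changes, the analysis section does not name that contrast, and the sample size best fits a 2-df interaction that cannot tell a T1-only difference from a lasting one. If that interaction decides, a 0.53 SD difference confined to T1 would make it significant in about 81% of trials at rho = 0.5 (about 66% to 96% for rho 0.3 to 0.7), against the 5% error rate of the T0-T2 contrast.

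These figures assume 106 analysed participants, sphericity, equal variances and no difference at T2. The correlation changes the percentages but not the conclusion, because the interaction is equally sensitive to all three patterns whatever its value. The documents do not establish that the authors would in fact claim success on a T1-only effect.

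**What to change.** In Statistical Analyses, name one confirmatory test: the arm difference in T0-to-T2 change in the TEX-Q total, as a 1-df contrast from the mixed model with treatment-by-time terms. T0, T1 and T2 enter as outcomes, the arms are constrained equal at T0, and the test is two-sided at .05. State that the T1 contrast, the overall interaction and the main effects are supportive. Use the same T2 contrast for the four secondary hypotheses in the Introduction, and say at which time points the post hoc tests apply.

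In Sample Size, restate power for this contrast and give the assumed correlation. At N = 106, rho = 0.5 and 0.53 SD, power is about 77% for the unadjusted change and about 88% with baseline adjustment, so the adjusted form keeps the planned size workable under those assumptions.

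The cost is a few sentences and one restated power figure, with no new data. The small downside is that an effect seen only at T1 no longer counts as primary success.

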### Randomization

Stratified permuted block randomization with a block size of 4 permutations will be used to randomize participants 1:1 to the OIC and TAU conditions. Stratification will be based on prior experience with psychotherapy (no vs positive vs negative prior experience) to ensure that individuals with heterogeneous treatment experiences are balanced in both arms. Before the first enrollment, the randomization sequences will be generated by a researcher who is not involved in the study conduction by using a web-based program. At the end of the first web-based study visit, the responsible study psychologist initially determines the type of prior experience with psychotherapy by evaluating the information given by each participant. The randomizing officer will then conduct the allocation of each pseudonymized study case according to the randomization plan. Finally, the randomizing officer will inform the respective study psychologist about the group membership on a case-by-case basis.

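### The T0 score is both a level of the repeated outcome and a candidate covariate in the same mixed model; under common covariance structures this makes the post hoc arm comparison at T2 anticonservative.

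*Protocol article*

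**What the plan says.** The protocol article, Statistical Analyses, gives the primary model one between-subject factor for treatment and "one within-subject factor time (T0, T1, and T2". T0 is therefore part of the outcome vector.

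The same paragraph has a covariate screen before modelling. The first candidates named are "additional variables (eg, respective baseline scores, type of prior experiences with psychotherapy"; prior knowledge, state anxiety and others follow. Each is checked for a significant association with the outcome concerned, and then: "If there are additional covariates, they will be included in the linear mixed model". Arm differences are to be examined with Tukey post hoc tests, or Bonferroni-corrected tests if group sizes are imbalanced.

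The section extends this strategy to the secondary outcomes, except capacity to consent, satisfaction with the information, and (serious) adverse events. The article names no covariance structure. The hypotheses at the end of the Introduction concern a greater change from T0 to T2 under OIC plus TAU than under TAU alone, which is an arm-by-time contrast.

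**The concern.** A baseline score can be a response or a predictor in such a model. Here the plan allows both at once. At T0 the covariate and the response are the same number, so the model fits T0 far better than T1 or T2. A structure with one common variance averages that artificially small T0 residual into the variance used for every visit. Arm comparisons at the post-randomisation visits then look more precise than they are. A structure with a separate variance per visit has a different problem: a slope of 1 makes the T0 residual exactly zero and the likelihood degenerates.

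The entry condition gives little protection, since one third of the outcome values are the candidate covariate. At stake are the visit-specific arm comparisons, which show when the consultation works. The same fault recurs for each secondary outcome in Table 1 that has a T0 value and is analysed by this model: decisional conflict, the side-effect items, autonomous motivation, adherence intention, and the interest and knowledge items.

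**Working it through.** **Inputs from the protocol article.** Two-sided α = .05 ("Each hypothesis will be tested two-sided with an α level of .05"); 1:1 allocation; 122 randomised, 61 per arm; outcome levels T0, T1, T2; Cohen f = 0.125.

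**Assumptions, because the article gives no figure.** Outcome standardised to variance 1, equal correlation ρ between visits over the range 0.3–0.9, complete data.

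**1. The plan's own figure.** For the within-between interaction with 2 groups and 3 measurements, λ = f²·N·3/(1−ρ) with 2 and 2(N−2) degrees of freedom. At ρ = 0.5 and N = 106, λ = 0.015625 × 106 × 3 / 0.5 = 9.94 and power is 0.807. At N = 104 power is 0.799. So 106 is the smallest even N reaching 80%, and 106 × 1.15 = 121.9, which rounds to 122. The stated size reproduces, with the interaction over three measurements as its basis.

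**2. Standard error at T2 with T0 in both roles, compound symmetry.**

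- Pooled slope on the T0 score: b = (1 + 2ρ)/3
- Residual variance at T0: (1 − b)²
- Residual variance at T1 and T2: 1 − 2bρ + b²
- Variance the model uses at every visit: the mean of the three
- SE ratio (model to true) = √(mean / T2 variance); type I error = 2·[1 − Φ(1.96 × ratio)]

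| ρ | b | T0 variance | T2 variance | Mean | SE ratio | Type I error |
|---|---|---|---|---|---|---|
| 0.3 | 0.533 | 0.218 | 0.964 | 0.716 | 0.861 | 9.1% |
| 0.5 | 0.667 | 0.111 | 0.778 | 0.556 | 0.845 | 9.8% |
| 0.7 | 0.800 | 0.040 | 0.520 | 0.360 | 0.832 | 10.3% |
| 0.9 | 0.933 | 0.004 | 0.191 | 0.129 | 0.821 | 10.7% |

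At ρ = 0.5 the model SE is √(0.556 × 2/61) = 0.135, whereas the true value is √(0.778 × 2/61) = 0.160.

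**3. Simulation under no effect (REML, 61 per arm, unadjusted 5% test at T2).**

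- Compound symmetry: rejection 9.0%, 9.2%, 10.4% and 9.4% at ρ = 0.3, 0.5, 0.7 and 0.9.
- Random intercept, ρ = 0.5: 9.3%. AR(1) fit, ρ = 0.5: 10.1%.
- Diagonal and unstructured: the slope runs to 1 and the T0 variance to 0. With an artificial variance floor, rejection was 5.2% (diagonal) and 1.5% (unstructured; 200 runs, unstable). The fault there is a singular fit, not a doubled error rate.

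**4. The contrast that carries the hypothesis.** In balanced data a covariate that is constant over time cancels from the T2-minus-T0 difference. The within-subject variance stays at 1 − ρ with or without it. In the compound-symmetry fits this contrast was rejected in 4.4–5.1% of null trials.

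**5. After giving T0 one role.** T0 as covariate only (ANCOVA at T2): 4.9%, 5.2% and 5.0% at ρ = 0.3, 0.5 and 0.7. T0 as outcome level only: 5.1–5.3% for the change from T0 to T2, and 4.0% for the T2 arm difference in the compound-symmetry model at ρ = 0.5 (1,500 runs).

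**The case against.** The strongest reply is that the hypothesis under test is untouched. A reader might infer from error rates of 9–11% that the primary test is invalid. The documents do not support that: the hypothesis is change from T0 to T2 by arm, and step 4 shows that this contrast keeps its level. In simulations where the fitted structure was wrong for the data, the contrast under a compound-symmetry fit was rejected in 7.6–8.9% of null trials. That comes from the wrong structure, not from the covariate. This part of the objection stands in full.

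Second, the affected comparison is post hoc and the plan adjusts it. The article does not define the family, so the following is assumed. At ρ = 0.5, Bonferroni over three visits gives 2·[1 − Φ(2.394 × 0.845)] = 4.3% for the T2 difference alone, and Tukey over six cells gives about 1.5%. Over the three arm comparisons together, the error is about 8% with Bonferroni and about 3% with Tukey. So the 9–11% is a figure before adjustment. The standard error remains too small: the Bonferroni threshold should yield 1.7%, not 4.3%. If the adjusted family is only the two arms at one visit, the adjustment does nothing.

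Third, the covariance structure is not named, and an article may leave it to a fuller document. That makes the inflation conditional. It does not rescue the double use, since the diagonal and unstructured alternatives examined give a singular fit.

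Finally, two further harms might be attributed to the double use: a treatment main effect diluted by averaging over T0, and lower power for the interaction than for a baseline-adjusted analysis. Both follow from having T0 as an outcome level at all, with or without the covariate, and neither belongs to this point.

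**Conclusion.** The point holds in a limited form. The double use of T0 is a stated rule and selection of the baseline score is nearly certain. Under a random-intercept, compound-symmetry or AR(1) structure, the standard error of the post hoc arm difference at T2 is about 14–18% too small, and its type I error before multiplicity adjustment is about 9–11% instead of 5%. This rests on assumed correlations of 0.3–0.9, complete data and 61 per arm. Under a diagonal or unstructured covariance the model is singular.

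An unconditional statement that the plan doubles its type I error would go too far. It would require a covariance structure that the article does not name, and it would not apply to the T0-to-T2 contrast. For that contrast the cost is only that the intended baseline adjustment brings no benefit.

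**What to change.** Give T0 one role, in one of two ways:

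- Keep T0 as a level of time and delete the respective baseline scores from the list of candidate covariates. Optionally constrain the two arms to a common mean at T0.
- Model T1 and T2 only, with treatment × time and T0 score × time as fixed effects, and test the arm difference at T2.

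Use the same form for every secondary outcome that has a T0 value and is analysed by this model. T3 should not be added as part of this change: the plan leaves it out of both the model and the hypothesis.

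The cost is a change of model wording. No data collection, visit or sample size is affected.
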